## Abstract

**Background:**

Primary open-angle glaucoma (POAG) is a major cause of irreversible blindness worldwide, characterized by progressive optic neuropathy and loss of retinal ganglion cells (RGCs). Although lowering intraocular pressure (IOP) remains the mainstay of glaucoma management, many patients continue to experience vision loss, underscoring the need for adjunctive neuroprotective approaches. In Ayurveda,
*Rasayana* therapies are believed to slow degenerative processes. One such intervention is a Rasayana Formulation (RF) comprising three oral preparations; Rasayana Churna (RC), Saptamrita Lauha (SL), and Yashada Bhasma (YB). Additionally, topical Arka (distilled extract) of Shigru Pallava (SP) has been used traditionally for glaucoma and may have an IOP-lowering effect.

**Methods:**

This is an open-label, two-arm, parallel-group randomized controlled trial with a 2:3 (control: intervention) allocation ratio. A total of 50 previously or newly diagnosed POAG patients (IOP < 30 mmHg) are planned for enrollment. The control group receives the conventional standard of care alone, whereas the intervention group receives standard care plus RF (2.5 g, taken orally twice daily) and SP eye drops (1 drop, four times daily), administered for 90 days with a further 90-day follow-up. Primary outcomes include changes in optic nerve function measured by visual field indices (mean deviation (MD), pattern standard deviation (PSD), visual field index (VFI)) and retinal nerve fiber layer (RNFL) thickness, while secondary outcomes include IOP changes.

**Results:**

Participant recruitment and data collection are ongoing. Final outcomes will be disseminated in peer-reviewed journals.

**Conclusions:**

If shown to be effective, the combined RF and SP eye drops could enhance neuroprotection and further control IOP in POAG, thereby addressing a significant need in current glaucoma therapy. This trial may provide a foundation for larger-scale investigations into integrative treatments for glaucoma management.

**Trial Registration:**

Clinical Trial Registry of India (CTRI) no. CTRI/2023/06/053681, dated 08.06.2023.

Available from:
https://trialsearch.who.int/Trial2.aspx?TrialID=CTRI/2023/06/053681

**Protocol Version:** 3.0, dated 05.01.2023

## Introduction

Glaucoma is one of the leading causes of irreversible blindness worldwide, and its global prevalence is steadily increasing.
^
1
^ It is characterized by progressive degeneration of the optic nerve, resulting in corresponding visual field loss and eventual blindness if left untreated. Although the pathophysiology of glaucoma is multifactorial, open-angle glaucoma (OAG) is the most common clinical phenotype, defined by an open anterior chamber angle, characteristic optic nerve head changes, and progressive loss of peripheral vision followed by central visual field loss.
^
2
^ Elevated intraocular pressure (IOP) is a significant risk factor in OAG, though some patients may develop the disease without clinically elevated IOP.
^
3
^ Primary open-angle glaucoma (POAG), which lacks underlying secondary ocular disease, accounts for up to 75% of all glaucoma and remains one of the most prevalent and challenging forms to treat.
^
4
^ Current therapeutic approaches primarily aim to reduce IOP, as it is the only well-established method for slowing disease progression; however, multiple trials continue to evaluate novel diagnostic, management, and treatment strategies to address the multifactorial nature of POAG.
^
5
^

Despite the effectiveness of IOP-lowering therapies, many patients experience ongoing vision loss.
^
6,
7
^ Such observations highlight the need for neuroprotective strategies that either supplement or act independently of IOP reduction. Neuroprotection refers to interventions designed to prevent or delay glaucomatous neurodegeneration, chiefly by preserving retinal ganglion cells (RGCs).
^
8
^ In Ayurvedic medicine, diseases resembling glaucoma are correlated with “Adhimantha” and “Timira.” The Ayurveda concept of “Rasayana” signifies therapies that delay senile or degenerative changes, and “Chakshushya Rasayana” refers specifically to interventions intended to protect vision through supporting ocular tissues. By addressing both pathophysiological aspects and symptomatic presentations, these traditional approaches may offer additional benefits in glaucoma management.

POAG is now recognized primarily as an optic neuropathy, with specific pathophysiological features that differentiate it from other optic nerve diseases.
^
9
^ Although high-quality randomized controlled trials have demonstrated that lowering IOP can slow visual field deterioration, many patients still progress to blindness due to treatment limits or side effects.
^
10,
11
^ This has propelled further exploration of neuroprotective therapies independent of IOP lowering, focusing on maintaining RGC health.
^
12–
14
^ Preclinical studies have shown neuroprotective effects of various agents; yet, clinical investigations in humans remain inconclusive.
^
15
^ Memantine (an N-methyl-D-aspartate receptor antagonist) demonstrated benefit in other neurodegenerative diseases but showed no significant effect in glaucoma.
^
16
^ Brimonidine (an α2-adrenoreceptor agonist) exhibited potential in slowing visual field deterioration, though a controlled trial comparing 0.2% brimonidine with 0.5% timolol did not yield convincing evidence of neuroprotective efficacy.
^
17
^ Therefore, additional rigorous investigations into novel adjunctive therapies such as integrative Ayurveda-based interventions are warranted to address the remaining gaps in current glaucoma treatment.

Various Rasayana formulations are being used by Ayurveda practitioners in the management of ocular degenerative conditions such as glaucoma. The selected Rasayana Formulation (RF) in this study is a combination of three oral medicines: Rasayana Churna (RC), Saptamrita Lauha (SL), and Yashada Bhasma (YB). RC (an Ayurvedic herbal powder) has been traditionally used as a rejuvenating agent and is employed in a wide range of neurodegenerative conditions.
^
18
^ SL (an Ayurvedic herbal-mineral tablet) is a well-known classical formulation indicated in Timira (a term in Ayurveda used to describe certain stages of visual impairment).
^
19
^ YB (a purified, medicated nanoparticle preparation of zinc) is also indicated for eye diseases, as described in ancient texts of Rasa Shastra (Ayurvedic iatrochemistry), and is specifically referenced in the management of Timira.
^
20
^ Shigru Pallava (SP) Arka (distilled extract of
*Moringa oleifera Lam.* leaves) is used as eye drops by Ayurvedic ophthalmic practitioners in patients of glaucoma. Some studies have already been conducted on the use of SP Arka in POAG.
^
21,
22
^ The juice of SP is mentioned by Acharya Vagbhata as a therapeutic option in conditions like Adhimantha.
^
23
^ The Arka (distilled) form of SP is also detailed in Arka Prakasha, a classical treatise on the therapeutic applications of distilled Ayurvedic preparations.
^
24
^

## Protocol

### Objectives

**Primary objective:** To compare the neuroprotective activity of a RF (2.5 g administered twice a day) as an add-on therapy to the standard of care at 30, 60, and 90 days in patients with POAG.

**Secondary objective:** To compare the effect of SP eye drops [1 drop (0.05 mL)/eye] four times a day on IOP when used as an add-on therapy to the standard of care at 30, 60, and 90 days in patients with POAG.

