### Study design

This is an exploratory, open-label, two-arm, parallel-group randomized controlled trial with a 2:3 (control: intervention) allocation ratio. The total study duration for each participant is 180 days (90 days of intervention followed by 90 days of follow-up).

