### Limitations

The progression of neurodegeneration in POAG varies substantially among individuals, making small changes difficult to detect with precision. Moreover, because the RF and SP eye drops consist of multiple components, any observed benefits cannot be conclusively attributed to a single molecule or ingredient.

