### Outcomes

The primary outcome is the neuroprotective activity of the study interventions, measured by changes in optic nerve function, including alterations in VF indices (MD, PSD, VFI) and RNFL thickness. The secondary outcome comprises IOP changes assessed via tonometry, evaluating the potential ocular hypotensive effect of SP eye drops.

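### The objectives credit neuroprotection to RF and the IOP effect to SP drops, but the two-arm design identifies only the effect of the two given together

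*Protocol article*

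**What the plan says.** The Objectives section gives each component its own objective. The primary one is "To compare the neuroprotective activity of a RF (2.5 g administered twice a day) as an add-on therapy to the standard of care" and the secondary one is "To compare the effect of SP eye drops [1 drop (0.05 mL)/eye] four times a day on IOP when used as an add-on therapy", both at 30, 60 and 90 days.

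The Study design section describes an "open-label, two-arm, parallel-group randomized controlled trial with a 2:3 (control: intervention) allocation ratio". In the Abstract (Methods), "The control group receives the conventional standard of care alone", while "the intervention group receives standard care plus RF (2.5 g, taken orally twice daily) and SP eye drops". Table 1 under Interventions agrees: RF and SP drops are both listed for Group B, each for 90 days, and neither for Group A.

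The rest of the article does not keep to one target:

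- **Combination wording.** The Abstract's conclusion is about RF and SP drops combined. The first sentence of Outcomes defines the primary outcome for the study interventions jointly.
- **Component wording.** The IOP sentence of Outcomes speaks of "evaluating the potential ocular hypotensive effect of SP eye drops". The last paragraph of the Discussion and the title repeated under Reporting guidelines again assign neuroprotection to RF and the IOP effect to SP.

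The Limitations section, after noting that RF and SP each have several components, says that "any observed benefits cannot be conclusively attributed to a single molecule or ingredient".

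**The concern.** An objective should name an effect that the design can estimate. Here the objectives name two component effects, while randomisation varies both components together. A difference in visual field indices or RNFL could come from RF, from SP, or from the two acting jointly, and the data cannot tell these apart. The same holds formally for IOP.

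The primary objective is the more exposed of the two. SP is in the trial because it may lower IOP, and lower IOP is itself a route to better-preserved fields. The better the secondary hypothesis does, the harder it becomes to credit a field difference to RF. At stake is what the final report may say about each product, and what a later trial would carry forward.

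**Working it through.** **Inputs.** Two arms at 2:3 (Study design). Group A receives standard of care; Group B receives standard of care + RF + SP (Abstract, Table 1). The planned total is 50, with 20 control and 30 intervention (Sample size). The split agrees with the ratio: 50 × 2/5 = 20 and 50 × 3/5 = 30. No power calculation is given, and none is needed for this point.

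**Step 1: what one contrast contains.** For any outcome, write the mean as μ + ρ·RF + σ·SP + ι·RF·SP, where RF and SP are 0 or 1.

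- Group A (RF = 0, SP = 0): μ
- Group B (RF = 1, SP = 1): μ + ρ + σ + ι
- B minus A: ρ + σ + ι

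Adding any constant to ρ and subtracting it from σ leaves both group means unchanged. Only the sum is identified.

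**Step 2: rank check.** The design matrix with columns intercept, RF, SP and RF×SP, for 20 rows (1,0,0,0) and 30 rows (1,1,1,1), has rank 2 against 4 parameters. Without the interaction it has rank 2 against 3. More participants in the same two arms do not change the rank. For comparison, a 2×2 factorial has rank 4 of 4, and three arms (standard of care; + RF; + RF + SP) have rank 3 of 3 for additive effects.

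**Step 3: does the planned analysis help?** Statistical methods lists between-group tests of A against B and within-group repeated-measures tests. Neither separates RF from SP. No analysis plan could do so without further assumptions, because no participant is assigned one without the other.

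**Step 4: which assumptions would recover the component effects?** Use subscript F for field/RNFL and P for IOP.

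- The IOP contrast is ρ_P + σ_P + ι_P. It equals the SP effect σ_P if RF neither changes IOP nor modifies what SP does to it (ρ_P = ι_P = 0). The article neither states nor tests this.
- The field/RNFL contrast is ρ_F + σ_F + ι_F. It equals the RF effect ρ_F only if SP contributes nothing (σ_F = ι_F = 0). The article does not state this either, and its text points the other way. The Introduction says randomised trials have shown that lowering IOP can slow field deterioration. The Discussion suggests that SP drops may also act on ocular circulation and tissue, and it cites improved fields and IOP control when RF and SP were added together.

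The documents give no figure for how much of a field or RNFL difference an IOP change could produce over 90 days, so this contribution cannot be sized.

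**The case against.** Testing a combination as an add-on is a legitimate design, and the trial is labelled exploratory. The conclusion actually anticipated in the Abstract concerns the combination, and the 20 versus 30 comparison supports that. The Limitations sentence names RF and SP together and disclaims attribution to single ingredients. Since SP is the distillate of one plant, it could be read as already covering SP. The Introduction's rationale also admits protection that supplements IOP reduction as well as protection independent of it, so a partly IOP-mediated benefit is not outside the trial's purpose.

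Most of this stands, and it limits the point. It does not remove it. The Objectives, the IOP sentence of Outcomes, the end of the Discussion and the title still attribute effects to single components. The limitation stops at molecules and ingredients and never says that RF and SP cannot be separated. The exploratory label lowers the standard of evidence but does not make an unidentified effect estimable.

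A reader might infer that neither objective can be answered under any circumstances. That goes too far: the IOP contrast does estimate the SP effect if RF is assumed not to act on IOP. A reader might also infer that the sponsor has committed to concluding that RF alone is neuroprotective, or that protection is independent of IOP. The article states neither conclusion, and no objective or outcome claims independence from IOP.

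**Conclusion.** The objectives do not match the design. Of 50 planned participants, 0 are assigned RF alone or SP alone, and the design supplies one estimable treatment contrast per outcome where component attribution needs two or three. That contrast is the effect of RF plus SP added to standard of care.

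Reading it as an RF effect on field/RNFL requires that SP has no effect there, which the Introduction makes doubtful. Reading it as an SP effect on IOP requires that RF has no effect on IOP, which is untested. The primary objective is therefore the weaker of the two as worded.

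The randomised comparison is not invalidated, and arms, sample size and assessments can stay as they are. The matter is one of what is claimed. It should be fixed before results are reported.

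**What to change.** 1. **Objectives.** Restate the primary objective as the effect of RF plus SP drops, added to standard of care, on visual field indices and RNFL. Restate the secondary objective as the effect of the same combination on IOP.
2. **Alignment.** Bring the IOP sentence of Outcomes, the closing paragraph of the Discussion and the title-level wording into line, matching the Abstract's conclusion and the first sentence of Outcomes.
3. **Limitations.** Add that the effects of RF and SP cannot be separated, and that an IOP-mediated contribution to the primary outcome cannot be excluded.
4. **What not to add.** A model of field or RNFL adjusted for on-study IOP should not be offered as support for IOP-independent protection. It conditions on a post-randomisation mediator, which is also affected by discretionary standard care in an open-label trial. It would not separate RF from any effect of SP outside IOP.

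The cost is a wording amendment through the route in Protocol amendments, including a registry update, while recruitment is still under way. The claims become less specific. Keeping component-specific objectives would instead need a design that separates the two, such as a factorial or an additional arm, which is a much larger change and is not required for the restated objectives.

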### Study design

This is an exploratory, open-label, two-arm, parallel-group randomized controlled trial with a 2:3 (control: intervention) allocation ratio. The total study duration for each participant is 180 days (90 days of intervention followed by 90 days of follow-up).

### Participants and eligibility criteria

All newly diagnosed and untreated patients of POAG will be considered for inclusion if they meet the following criteria: (1) POAG with IOP < 30 mmHg; (2) age between 30 and 60 years; (3) open irido-corneal drainage angle on gonioscopy; (4) documented glaucomatous visual field defects in at least one eye, accompanied by corresponding optic nerve head damage; and (5) at least two reliable visual field (VF) examinations in the year, defined by a false response rate below 15% and a detectable blind spot.

Patients were excluded if they had a visual acuity worse than 6/36 in the study eye, congenital/early childhood glaucoma, secondary glaucoma (exfoliative, pigmentary, or neovascular), anterior segment abnormalities affecting IOP measurement, or a visually significant cataract. Other exclusion criteria included ocular conditions that could cause VF abnormalities (e.g., degenerative myopia, diabetic retinopathy, maculopathy); best corrected visual acuity (BCVA) below 0.5 Snellen decimal fraction (> +0.3 LogMAR); severe VF loss (mean deviation (MD) worse than −12 dB in the better eye or −15 dB in the worse eye); inability to use topical medical therapy; concurrent treatment for another ophthalmic condition; previous ocular surgery other than uncomplicated cataract extraction, YAG laser capsulotomy, or laser glaucoma surgery (argon or selective laser trabeculoplasty); pregnancy or breastfeeding; medical unfitness for the trial; or participation in any other interventional research study.

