### Concomitant care and interventions

Participants will continue using standard anti-glaucoma medications, such as beta-blockers, prostaglandin analogs, or carbonic anhydrase inhibitors, as prescribed by treating ophthalmologists, unless contraindicated. Introduction of any new Ayurvedic formulation with overlapping ingredients or additional investigational drugs will be prohibited. Additionally, participants will be advised to maintain consistent dietary and lifestyle habits throughout the trial and to refrain from using any unauthorized herbal or nutraceutical supplements.

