^ Nicotinamide supplementation also appears promising, mitigating mitochondrial dysfunction and RGC death in mouse models susceptible to glaucoma.
^
32
^ However, clinical investigations focusing on neuroprotective strategies in modern medicine face challenges such as high dropout rates and limited efficacy, as evidenced by inconsistent results in brimonidine trials (e.g., LoGTS) and memantine’s failure to significantly slow glaucoma progression in phase III human studies.
^
16,
30,
31
^

Ayurvedic clinical trials have shown favorable outcomes when standard antiglaucoma regimens are supplemented with oral RF and SP eye drops.
^
21,
22
^ Improved visual acuity, better control of IOP, and enhanced VF have been observed. Given these encouraging findings, the present exploratory randomized controlled trial is designed to rigorously assess the neuroprotective capabilities of the specified RF, alongside the effect of SP eye drops on IOP, in patients with POAG who are already receiving conventional care. By systematically evaluating changes in IOP, RGC function, and structural markers such as RNFL thickness, this study aims to help bridge gaps in current knowledge and support the development of integrative, evidence-based treatments for glaucoma. If these methods demonstrate efficacy, future large-scale trials could further validate Ayurvedic interventions as a valuable adjunct to traditional glaucoma management.

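### The protocol describes its population inconsistently (untreated new cases, known cases, patients already on treatment); if both kinds enter, the IOP comparison loses precision and within-arm IOP change is confounded with starting standard care

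*Protocol article*

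**What the plan says.** Four parts of the protocol article bear on who is enrolled.

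- **Participants and eligibility criteria:** "All newly diagnosed and untreated patients of POAG will be considered for inclusion". This is the operative entry sentence, and it limits the trial to new, treatment-naive cases.
- **Abstract, Methods:** "A total of 50 previously or newly diagnosed POAG patients (IOP < 30 mmHg) are planned for enrollment". Known cases are included here.
- **Discussion:** the trial is described as being "in patients with POAG who are already receiving conventional care".
- **Concomitant care and interventions:** "Participants will continue using standard anti-glaucoma medications".

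The exclusion list also makes an allowance for earlier laser treatment of glaucoma. It excludes "previous ocular surgery other than uncomplicated cataract extraction, YAG laser capsulotomy, or laser glaucoma surgery (argon or selective laser trabeculoplasty".

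The same paragraph has two acuity exclusions. One reads "Patients were excluded if they had a visual acuity worse than 6/36 in the study eye", with the type of correction not stated. The other is "best corrected visual acuity (BCVA) below 0.5 Snellen decimal fraction (> +0.3 LogMAR", with the eye not stated.

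Table 1 gives standard care to both arms. The Outcomes section makes IOP change the secondary outcome. The Statistical methods section plans RM-ANOVA within each arm, IOP included, and an unpaired t-test or a nonparametric alternative between arms. The Randomization section describes variable blocks at 2:3 and states no stratification factor.

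**The concern.** Treatment status at entry determines what an IOP change means in this trial. In a patient starting standard care at about baseline, pressure falls because of that care, with or without the study drops. In a patient already treated, most of that fall has happened before baseline. The 30 mmHg entry limit likewise means off-treatment pressure in one case and on-treatment pressure in the other, and an add-on effect is an addition to newly started care in one and to established care in the other.

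If the entry text and the abstract are applied by different people or at different times, the trial may enrol a mixture that no section describes. Three things are then at stake: the precision of the between-arm IOP comparison, the reading of the within-arm IOP analysis, and the ability to say to whom the result applies.

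**Working it through.** **Step 1. Compare the statements.** The eligibility sentence requires a new diagnosis and no treatment. The abstract allows known or new diagnosis, so the entry sentence describes a subset of it: the two are inconsistent but not exclusive. The Discussion has patients under treatment on entry, which cannot be squared with untreated. The concomitant-care sentence and the laser allowance point the same way as the Discussion, but less firmly. The former could describe use during the trial, and the latter only stops prior laser from excluding someone; it does not admit a patient who fails the entry sentence.

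**Step 2. The plan's own figure.** The sample size of 50 is given with no alpha, power, effect or SD, so it cannot be reproduced. The parts agree: 20 + 30 = 50, and 20:30 is 2:3.

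**Step 3. Precision under a mixture.** The following inputs are assumptions, not in the article: SD of IOP change within each stratum s = 3 mmHg; extra fall from starting standard care g = 3, 5 or 7 mmHg, the same in both arms; untreated fraction f = 0.5; two-sided 5% test; normal approximation. The arm sizes, 20 and 30, are the protocol's.

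- SD of change = √(s² + f(1−f)g²)
- SE of the difference = SD × √(1/20 + 1/30) = SD × 0.2887
- Difference detectable with 80% power = SE × (1.960 + 0.842)
- Power for 2 mmHg = Φ(2/SE − 1.960)

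| Population | SD (mmHg) | Detectable difference (mmHg) | Power for 2 mmHg |
|---|---|---|---|
| One kind only | 3.0 | 2.4 | 64% |
| Half untreated, g = 3 | √(9 + 2.25) = 3.4 | 2.7 | 54% |
| Half untreated, g = 5 | √(9 + 6.25) = 3.9 | 3.2 | 43% |
| Half untreated, g = 7 | √(9 + 12.25) = 4.6 | 3.7 | 32% |

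An even split is the worst case. At one quarter or three quarters untreated, the SD is 3.3 to 4.3 mmHg and power 56% to 37%.

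**Step 4. Bias and the within-arm reading.** A simulation of 20,000 trials with f = 0.5, g = 5, s = 3 and no add-on effect gave a mean between-arm difference of −0.01 mmHg and a type I error of 4.9% for the unpaired t-test. The intervention arm alone showed a mean fall of 2.5 mmHg, as expected from f × g = 0.5 × 5. For g = 3 to 7 that fall is 1.5 to 3.5 mmHg, all of it from standard care.

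**Step 5. Acuity.** LogMAR = −log10(decimal). 6/36 = 0.167, giving 0.78; 0.5 gives 0.30, which agrees with the article's own conversion. If both limits are best-corrected and apply to the same eye, the 0.5 rule already removes everyone the 6/36 rule would. If 6/36 is unaided or presenting acuity, or the eyes differ, both can stand.

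**The case against.** The strongest reply is that randomisation deals with this. Both arms receive standard care, allocation is random, and a between-group comparison is planned. That stands. A reader might infer that IOP change becomes uninterpretable, but step 4 shows that the mixture neither biases the between-arm contrast nor inflates its error rate. The simulation does take standard care to work equally in both arms.

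A reader might also infer that chance imbalance in prior treatment is a further hazard on top of the lost precision. It is not. With f = 0.5, the imbalance has SD √(0.25 × (1/20 + 1/30)) = 0.144, worth 0.144 × 5 = 0.72 mmHg at g = 5. The added variance contributes √(6.25 × (1/20 + 1/30)) = 0.72 mmHg to the standard error. These are the same quantity, and the t-test already carries it.

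Nor do the acuity limits contradict each other. Exclusions apply jointly, so failing either removes the patient; what is unclear is which correction and which eye each refers to.

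It can be said that covariates belong in an analysis plan that is not shown. That is fair for silence, but the article names the unpaired t-test, so the choice is open to comment. It is also fair that Table 4 collects medical history at screening, so treatment status may already be on file, and that IOP is a secondary outcome of an exploratory trial. None of this settles which population is meant.

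**Conclusion.** The inconsistency is real and unresolved in the article. The firm conflicts are between the eligibility sentence and the abstract on diagnosis, and between the eligibility sentence and the Discussion on treatment; the concomitant-care sentence and the laser allowance are secondary support.

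If both kinds of patient are enrolled, the cost is lower precision for IOP, a within-arm IOP change that cannot be read as an effect of the Shigru Pallava drops, and doubt about whom the result describes. The size of the precision loss rests wholly on assumed inputs: a 3 mmHg within-stratum SD, a 3 to 7 mmHg fall from starting standard care, and an even split, which is the least favourable. If only one kind is enrolled in practice, there is no such loss and what remains is wording. The acuity point is minor drafting. The documents do not show which population or acuity rule is intended, and this review does not choose one.

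**What to change.** 1. Reconcile the abstract, the eligibility section, the concomitant-care section and the Discussion to one statement of diagnosis and treatment status at entry, and say whether the 30 mmHg limit is on or off treatment.
2. If both untreated and treated patients are being recruited, record treatment status and prior laser on the CRF before the envelope is opened.
3. In that case, replace the unpaired t-test for IOP with a between-arm model adjusted for baseline IOP and that factor. On the assumptions above, adjusting for the factor brings the residual SD back to about 3.0 mmHg.
4. State that within-group IOP change will not be interpreted as an effect of the drops.
5. For each acuity exclusion, state the correction and the eye.

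The cost is an eligibility wording amendment while recruitment is under way, one CRF field, and about two degrees of freedom in the model. Patients already enrolled can be classified from the medical history taken at screening.
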